#### Points and rankings

Points could be earned by logging in to the game, breaking through levels, reading articles or watching videos, etc. The point for logging in is 1, once a day. Points for breaking through levels is 5 for the first level, 10 for the second level, 15 for the third level, and so on, and may only be accumulated once a day. Two points can be awarded for reading an article or watching a video for more than 30 s. One point could be earned each time if they pick up a condom or antiviral medicine during the game, and the points can be accumulated. The points and rankings of themselves and their friends in the game can be viewed.

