### Intervention group: overview

#### AIDS fighter · health defense intervention group 1

Participants will receive the educational game “AIDS Fighter · Health Defense” and will be required to play the game and learn AIDS education essays or videos in the “knowledge corner” at least 5 days a week and 20 min a day. A data management system will be used to monitor the time participants played in the game, and whether they have learned the content in the “knowledge corner”. After four weeks of intervention, the effect of the intervention will be evaluated by using the same questionnaire as applied in the baseline survey.

Participants will be informed that they will be recognized and rewarded after completing daily game tasks and completing four-week follow-up assessments according to the points ranking. The top 20% will receive a “Gold Award” and 50 RMB in cash, the middle 30% will receive a “Silver award” and 50 RMB in cash, and the lowest 50% will receive a “Bronze award” and 20 RMB in cash.

#### AIDS fighter · health defense intervention group 2

Participants will receive “AIDS Fighter · Health Defense”, without limitation in time to play the game or learn the content of the “knowledge corner”, and there are no incentives as recognition or rewards. Participants play this game according to their preference. Four weeks later, the same questionnaires will be used to measure the effect of their use of the game.

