### Recruitment, randomization, and allocation concealment

#### Recruitment

Participants will be recruited through online recruitment and on-site recruitment. The sufficient statistical power to detect changes in AIDS knowledge, attitude and behaviors after the intervention are considered in sample size calculation, and131 participants are need in each group to maintain 80% statistical power. Assuming the attrition rate is 10%, the sample size of each group is determined to be 145, and the total sample size is 580.

The study site is Luzhou City, Sichuan Province, China. Participants will be recruited from secondary school, high school, college and university. When they agree to participate in the research and complete the follow-up measurement and informed consent form will need to be signed for confirmation. After completing the research, each participant will receive a reward of 30 RMB in cash.

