#### Randomization and allocation concealment

Opaque envelopes will be prepared for randomization. In 580 envelopes, each will contain a note with the words “ AIDS Fighter · Health Defense Intervention Group 1” or “ AIDS Fighter · Health Defense Intervention Group 2” or “Control Group 1” or “Control Group 2” (145 envelopes per group). Participants will be randomized to select an envelope, then assigned to the corresponding group according to the information on the envelope. The data analysts are blinded to the allocation.

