Four arms were designed in our research, including two intervention arms and two control arms. Participants in the two intervention groups will receive AIDS Fighter · Health Defense, one of which will strictly control the time spent in the game and provides incentives to increase motivation to use the game; Another group will receive AIDS Fighter · Health Defense, but without time limitation or incentives; One of the two control groups is classroom teaching and the other is autonomous learning. By comparing the intervention groups with the control groups, it can be found whether AIDS Fighter · Health Defense is better than classroom teaching and autonomous learning in improving participants’ AIDS prevention ability; By comparing the two intervention groups, we can figure out whether AIDS Fighter · Health Defense is attractive, whether players will voluntarily use the game to improve AIDS prevention capabilities. This will determine whether the game can be promoted on a large scale. By comparing the two control groups, we can understand the difference between classroom learning and autonomous learning in improving AIDS prevention capabilities. Such a design could see the differences in the effects of game-based intervention, classroom teaching, and independent learning in AIDS education. And provide evidence for choosing different AIDS education methods.

We hope that the game-based interventions can be widely used in AIDS education in China and other countries. However, some countries are exam-oriented in evaluating the effect of education and there may be some resistance to the promotion and application of the game; parents may worry that their children will be addicted to the game and affect their academic performance [26, 27]. To address this problem, we can perform identity authentication when the player enters the game and prevent minors from being addicted to the game by limiting the online time.

“AIDS Fighter · Health Defense” could be suitable for the public, high-risk groups of AIDS, and HIV-infected people. It could be an auxiliary educational tool for AIDS prevention for the public and high-risk groups, and for HIV-infected people to maintain long-term ART adherence and keep virus suppression. We believe that with the development of this study, we can provide an AIDS education method for China and other countries to improve the ability to prevent AIDS of public and the quality of life of HIV infected.

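### Friends' points and rankings are visible with no stated limit by arm, so the paid game arm may influence the voluntary-use arm, and control participants may reach the game

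*Protocol article*

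**What the plan says.** **Setting and allocation.** Under Recruitment: "The study site is Luzhou City, Sichuan Province, China", and "Participants will be recruited from secondary school, high school, college and university". Under Randomization and allocation concealment, 580 envelopes are prepared, 145 per arm: "Participants will be randomized to select an envelope, then assigned to the corresponding group according to the information on the envelope". No school or class enters the allocation.

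**The game.** Under Points and rankings: "The points and rankings of themselves and their friends in the game can be viewed". Game data management lists what the system collects, including basic personal information, points, quiz answers, log-in times and length of use.

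**The two game arms.** Under Intervention group: overview, group 1 must play at least 5 days a week for 20 minutes a day. Its members are told that they will be recognised and rewarded after "completing daily game tasks and completing four-week follow-up assessments according to the points ranking". Group 2 gets the same game, but "there are no incentives as recognition or rewards. Participants play this game according to their preference".

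**The controls.** Under Control group: overview, control group 1 has weekly classes and control group 2 has the knowledge-corner material in a chat group without gamification.

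**What the contrasts are for.** Study design hypothesises no difference between the two game groups and better results in the game groups than in the controls. The Discussion uses group 1 versus group 2 to judge whether adolescents will use the game of their own accord, and says this will decide whether it can be rolled out widely.

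**The concern.** Group 2 is informative only if its members play for the game's own appeal. With individual allocation in a shared student population, friends can land in different arms. If the friends' display crosses arms, a group 2 player sees the activity of group 1 friends who are obliged to play and rewarded by rank. Table 1 of the article itself gives the points ranking as something that motivates play. Group 2's use would then partly reflect group 1's incentives. Because the hypothesis for this pair is no difference, spill-over that makes the arms alike could appear to confirm it.

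The second route runs to the controls. The Background reports from earlier trials that adolescents are readier to recommend game-based AIDS education to friends. The article states nothing that keeps classroom or chat-group participants out of the game. Any who play bring their arm closer to the game arms and shrink the contrast. The sample size allows for attrition but not for such a loss.

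**Working it through.** **1. The plan's own figures.** Recruitment gives 131 per group for 80% power, 10% attrition, 145 per group and 580 in total.
- 131 × 1.10 = 144.1, rounded up to 145; 4 × 145 = 580. Both reproduce.
- Dividing instead, 131 / 0.90 = 145.6, gives 146. The difference of one is immaterial here.
- No effect size or standard deviation is stated, so 131 itself cannot be reproduced.

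**2. Effect implied by 131 per arm.** Assumed: a comparison of two means, two-sided 0.05 (the article gives 0.05 without sidedness), normal approximation.
- d = (1.960 + 0.842) × √(2/131) = 2.802 × 0.1236 = 0.346.

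**3. Dilution.** Let c be the share of the contrast that is lost, so the expected difference is d(1 − c). The documents give no value; 10% to 30% is assumed. If a share p of controls plays and each receives a fraction r of the game's effect, then c = p × r. For example, p = 20% and r = 50% give c = 10%.

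Power = Φ(d(1 − c)√(n/2) − 1.960), where n is the number per side. At c = 0, d√(n/2) is 2.802 for n = 131 and 3.962 for n = 262.

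| c | d(1 − c) | Power, 131 v 131 | Power, 262 v 262 |
|---|---|---|---|
| 0 | 0.346 | 80% | 98% |
| 10% | 0.312 | 71% | 95% |
| 20% | 0.277 | 61% | 89% |
| 30% | 0.242 | 50% | 79% |

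The last column takes both game arms against both control arms, one reading of the second hypothesis, with the same d and the same loss in both control arms.

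**4. Group 1 versus group 2.** No arithmetic applies. Side by side, the sections give: individual allocation; one game with friends' rankings visible; required play and rank-based reward in group 1; preference-led play without reward in group 2; and a conclusion about voluntary use drawn from comparing the two. No section says that the display is divided by arm.

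**5. Access and records.** Identity checks appear only in the Discussion, as a possible answer to game addiction: "we can perform identity authentication when the player enters the game". They are not set as a trial procedure. The data in Game data management would, however, show a control participant who logged in under their own details. They would miss play on a friend's account.

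**The case against.** **Much is inferred.** The article gives neither the number of schools nor recruitment by class, so mixing of friends across arms is likely but of unknown density. It does not say how friends are linked or whether the display pools the arms. Group 1's awards are percentage bands described under that group alone, so the reward ranking may be computed within the arm. This stands: the point is a risk left open by the design as described, not a demonstrated fault.

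**The direction for group 2 is not fixed.** A reader might infer that group 2's play and scores must be pushed up. Seeing required players far ahead could equally discourage voluntary players. The documents settle neither, so no more than a possible bias towards no difference can be claimed.

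**Exposure is partly recordable.** A reader might infer that contamination of controls would leave no trace. The system's log-in and personal data contradict this for play on a participant's own account. What is missing is a stated use of those records for this purpose, and any way to detect shared accounts.

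**The power loss is easily overstated.** All arms receive similar content, and control group 1 the same total time as group 1, so spill-over concerns delivery and incentive. Casual exposure need not carry the full effect. The pooled comparison is also far less sensitive. Both objections stand, and c is therefore treated as an unknown net loss.

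**It is an article.** Account set-up may be described in the full protocol. That is fair for log-in details. But the ranking display is described here as a feature of the game, and it sits awkwardly with the stated purpose of group 2.

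**Conclusion.** The point holds as a risk that is cheap to remove. Run as described, the game can carry group 1's incentives into group 2 through the friends' rankings, and this may favour the hypothesised absence of a difference in the comparison meant to test voluntary use. Control participants may also reach the game, which would dilute the game-versus-control contrasts by an unknown amount.

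As an illustration, a 10% to 30% loss of contrast takes a single two-arm comparison from 80% power to between 71% and 50%. The pooled comparison still has about 79% at 30%. These figures rest on the implied d of 0.346, a two-sided 0.05 test and an assumed loss.

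The documents do not show that every contrast is blurred: the case is not made for control group 1 versus control group 2. Nor is group 2 wholly unpaid, since every participant receives 30 RMB on completion; what it lacks is reward for play. Individual randomisation remains a legitimate choice.

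**What to change.** 1. During the trial, show each player points and rankings for their own arm only, and say so under Points and rankings.
2. Open log-in during the trial only to the study IDs of participants allocated to the two game arms.
3. Match the management system's log-in records to the allocation list. Add one item to the four-week questionnaire asking control participants whether they saw or played the game, to catch use of a friend's account. Report the result with a contamination sensitivity analysis, keeping intention-to-treat as the main analysis.

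The cost is a setting in a system the team already manages, one questionnaire item and one additional analysis. Allocation and sample size stay as they are. The downside is that players see fewer friends, so the ranking, which is part of the intervention's motivational content, may be slightly less engaging.

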#### Game data management

Educational resources can be edited and upload to the “knowledge corner” through the management system, and the system can realize the following data collection functions:1) Player’s basic personal information; 2) Player’s points and rankings; 3) Player’s message and consultation information; 4) Player’s answers to questions; 5) When did the player log in to the game and how long has it been used; and 6) What did the players learn in the “knowledge corner”.

### Intervention group: overview

#### AIDS fighter · health defense intervention group 1

Participants will receive the educational game “AIDS Fighter · Health Defense” and will be required to play the game and learn AIDS education essays or videos in the “knowledge corner” at least 5 days a week and 20 min a day. A data management system will be used to monitor the time participants played in the game, and whether they have learned the content in the “knowledge corner”. After four weeks of intervention, the effect of the intervention will be evaluated by using the same questionnaire as applied in the baseline survey.

Participants will be informed that they will be recognized and rewarded after completing daily game tasks and completing four-week follow-up assessments according to the points ranking. The top 20% will receive a “Gold Award” and 50 RMB in cash, the middle 30% will receive a “Silver award” and 50 RMB in cash, and the lowest 50% will receive a “Bronze award” and 20 RMB in cash.

#### AIDS fighter · health defense intervention group 2

Participants will receive “AIDS Fighter · Health Defense”, without limitation in time to play the game or learn the content of the “knowledge corner”, and there are no incentives as recognition or rewards. Participants play this game according to their preference. Four weeks later, the same questionnaires will be used to measure the effect of their use of the game.

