### Control group: overview

#### Control group 1

Participants will receive classroom teaching once a week for 100 min each time. The total time is the same as the time required by the AIDS Fighter · Health Defense intervention group 1. A regular teacher will conduct AIDS prevention classroom education on a fixed day each week and the content of the lecture is consistent with the knowledge in the game.

#### Control group 2

Participants will be added to the QQ chat group (one of the most popular social tools in China), and the same educational resources as the “knowledge corner” in AIDS Fighter · Health Defense will be uploaded to the QQ group. Participants will then be reminded to learn the knowledge by themselves daily. But there are no gamification elements, such as barriers, points ranking, answering questions, rewards, etc.

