### Outcomes and data collection

The primary outcomes are AIDS-related knowledge, AIDS-related stigma attitude and AIDS-related behaviors attitude before and four weeks after the intervention. AIDS-related knowledge will be assessed through a self-made questionnaire with a total of 45 items, one point for a correct answer. The higher the score, means the more knowledge participants have learned. AIDS-related behaviors attitude will be assessed through a questionnaire with eight items, with one point for a correct answer. The higher the score, means the lower the risk of AIDS-related behaviors among participants. Five experts were invited to verify the content validity of these questionnaires, the item-level CVI (I-CVI) and the scale-level CVI (S-CVI) are both 1. 00. AIDS-related stigma attitude will be assessed through the Chinese version of Zelaya’s HIV/AIDS Stigma Scale, which was compiled by Zelaya [16], with 24 items in total, and was Sinicized by Xing Haiyan [17]. After Sinicization, the I-CVI was 0. 82 ~ 1. 00, and the S-CVI was 0. 97. Each item uses a score of 1–5. The higher the score, the more the participants’ stigma of AIDS.

Secondary outcomes are the AIDS-related behaviors followed up for three and six months after the intervention. Participants will receive cash rewards after completing the evaluation. AIDS-related behaviors will be assessed through the Questionnaire on the Health of Young Students that was issued by the Chinese Center for Disease Control and Prevention, which has 33 items and is the official questionnaire for the investigation of AIDS-related behaviors among adolescents in China. The fewer AIDS-related risk behaviors, the more the participants have gained AIDS prevention capabilities.

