### Data management and statistical analysis

All data will be directly recorded in the online database (www.wjx.cn, Ranxing information technology co., Ltd., Changsha, China). The database system automatically saves the data and ensures the safety, integrity and consistency of the data. The web server is hosted in Alibaba Cloud (Alibaba Group, Hangzhou, China) and is protected by a corporate firewall, while a daily backup mechanism can ensure data security. Data has multi-level permission settings and password protection to ensure data security. In statistical analysis, general statistical analysis will be carried out by using standard statistical software and professional statistical software.

Analysis of Variance (ANOVA) will be used to find out whether there have differences between the AIDS Fighter · Health Defense intervention groups and the control groups in AIDS-related knowledge scores and attitude scores after the intervention of four weeks. Repeated Measures ANOVA will be used to see whether there have differences on the incidence of AIDS-related behaviors followed up for three and six months after the intervention in four arms. Intention-to-treat analysis will be used to account for the influence of attrition. The difference was statistically significant when *P* ≤ 0. 05.

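### Group 1 alone has an extra cash award partly conditional on the 4-week primary assessment, which risks unequal retention by arm that intention-to-treat does not repair

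*Protocol article*

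**What the plan says.** Five places in the protocol article bear on this point.

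- **Intervention group: overview, group 1.** Participants are told that "they will be recognized and rewarded after completing daily game tasks and completing four-week follow-up assessments according to the points ranking". The gold tier (top 20%) and the silver tier (next 30%) each carry 50 RMB, and "the lowest 50% will receive a “Bronze award” and 20 RMB in cash".
- **Intervention group: overview, group 2.** Participants get the same game, but "there are no incentives as recognition or rewards".
- **Control group: overview.** For control group 2, "But there are no gamification elements, such as barriers, points ranking, answering questions, rewards, etc". No reward is mentioned for control group 1.
- **Recruitment, and Outcomes and data collection.** The first says "After completing the research, each participant will receive a reward of 30 RMB in cash". The second, in its paragraph on the 3- and 6-month outcomes, says "Participants will receive cash rewards after completing the evaluation" without naming an arm or an amount.
- **Data management and statistical analysis.** Knowledge and attitude scores at four weeks are to be compared by ANOVA, and "Intention-to-treat analysis will be used to account for the influence of attrition".

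The primary outcomes are measured at baseline and four weeks. The sample size assumes a single 10% attrition rate for all four groups.

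**The concern.** The group 1 award is meant to encourage play, and the Discussion presents incentives as part of what separates the two game arms. As worded, though, it also rewards handing in the 4-week questionnaire, and that has nothing to do with whether the game works. One arm then has a stronger financial reason than the others to supply primary-endpoint data.

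If the share of participants who answer differs by arm, and answering is related to score, the arms are compared on differently selected subsets. The group 1 versus group 2 comparison (first hypothesis in Study design) is the most exposed, because the award is one of the differences between those arms.

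The article's stated safeguard does not meet this risk. Intention-to-treat settles who belongs in the analysis and under which arm. It does not say what score to use for someone who never completed the questionnaire. Without a further method, an ANOVA of 4-week scores uses only those who answered.

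**Working it through.** **The plan's own figures.** The article takes 131 per group, allows 10% attrition and states 145 per group, 580 in all.
- 131 × 1.10 = 144.1, rounded up to 145. By the other convention, 131 / 0.90 = 145.6, rounded up to 146. The stated 145 is within rounding of both, and 4 × 145 = 580.
- The 131 itself cannot be reproduced, because no effect size or SD is given. For two arms, two-sided 5% (sidedness assumed) and 80% power, it corresponds to (1.960 + 0.842) × √(2/131) = 0.346 SD.

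**Size of the extra award.** If the tiers apply as stated:
- Mean award = 0.20 × 50 + 0.30 × 50 + 0.50 × 20 = 35 RMB.
- A group 1 completer receives 20 + 30 = 50 RMB or 50 + 30 = 80 RMB, on average 65 RMB. The other arms have the common 30 RMB. The unassigned cash in Outcomes and data collection is left out, since it cannot be attributed to an arm.

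**Illustrative completer bias.** Assume that the propensity to answer is a normal latent variable with correlation ρ to the 4-week score, scored so that higher is more favourable. With retention r and cut-off k = Φ⁻¹(1 − r), the mean of completers exceeds the mean of all randomised by ρ × φ(k) / r SD. The article supplies neither ρ nor retention by arm, so both are assumptions.

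| Retention r | φ(k) / r | ρ = 0.3 | ρ = 0.5 |
|---|---|---|---|
| 95% | 0.103 / 0.95 = 0.109 | 0.033 | 0.054 |
| 90% | 0.175 / 0.90 = 0.195 | 0.058 | 0.097 |
| 80% | 0.280 / 0.80 = 0.350 | 0.105 | 0.175 |

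Differences between an arm at 95% and another arm (from unrounded values):
- 95% versus 90%: 0.026 SD (ρ = 0.3) to 0.043 SD (ρ = 0.5), about 7% to 12% of 0.346.
- 95% versus 80%: 0.072 SD to 0.121 SD, about 21% to 35% of 0.346.

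The 90% is the article's planned retention. The 80% doubles the planned attrition and is a pessimistic case.

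**Cross-check by a simpler model.** Let dropouts be worse than completers by 0.25, 0.5 or 1.0 SD. The bias is then the difference in dropout proportions times that gap. With 145 randomised per arm and no true effect:
- 5% versus 10% dropout: bias 0.013, 0.025 or 0.05 SD; rejection rate 5.1%, 5.5% or 6.9% instead of 5%.
- 5% versus 20% dropout: bias 0.038, 0.075 or 0.15 SD; rejection rate 6.0%, 9.2% or 22.2%.
- Equal 10% dropout: no bias, 5.0%.

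Power at 0.346 SD stays between about 78% and 81% in all these cases, so the issue is bias and not sample size.

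**Pooled comparison.** If the two game arms are pooled with equal weight against the pooled controls, and only group 1 retains differently, the shift is halved: 0.013 to 0.022 SD in the milder case and 0.036 to 0.060 SD in the pessimistic one.

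**The case against.** Several objections have force.

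- **Everyone is paid something.** A reader might infer that only group 1 is paid for the 4-week assessment. The article does not support that. All arms receive 30 RMB on completing the research, of which the 4-week visit is part, and a further sentence promises cash after the evaluation without naming an arm. What stands is that group 1 alone has an additional payment expressly tied to the 4-week assessment.
- **Differential attrition is not certain, and its direction is open.** A reader might infer that differential attrition is built in and that every contrast with group 1 is biased against it. The article gives no attrition by arm. Group 1 must also play at least 20 minutes a day on five days a week under monitoring, which could raise its dropout. If group 1 retained fewer people, the signs above would reverse.
- **The mechanism may be weaker than it looks.** The award requires the daily tasks as well as the assessment. Read literally, someone who has stopped playing has already lost it and gains nothing extra by answering. On the other hand, the tiers add to 100%, and the article does not say whether they cover the whole group or only those who met both conditions.
- **The incentive is deliberate.** The Discussion treats it as a design contrast meant to increase use of the game. That justifies rewarding play. It does not require the reward to depend on the outcome questionnaire.
- **Missing-data methods usually sit in an analysis plan.** This is right, and the absence of a named method is not the point here. Intention-to-treat could be carried out with imputation. What is open to criticism is the sentence that offers intention-to-treat itself as the remedy for attrition.

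**Conclusion.** The point holds as a risk. Group 1 alone has an extra award, averaging 35 RMB on top of the common 30 RMB, that depends in part on completing the primary-endpoint assessment. This could make 4-week retention differ by arm, by an amount and in a direction that the article does not determine. Intention-to-treat, as invoked, would not correct the result.

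The likely size is modest if retention stays near plan: 0.026 to 0.043 SD at 95% versus 90%. It becomes material, at 0.07 to 0.12 SD, only if another arm falls to 80%. These figures rest on assumed retention rates, on assumed correlations of 0.3 to 0.5 and on a single latent propensity common to all arms. They show scale and are not a forecast. The larger range should not be quoted alone, because it needs twice the planned attrition.

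The change is still worth making, because the risk is avoidable at almost no cost and sits at the primary endpoint.

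**What to change.** 1. **Award.** Make the group 1 award depend on game play and points only, and remove completion of the 4-week assessment from its conditions. Game data management already provides for logging points, log-ins and time used, so the questionnaire is not needed to determine the award. The intended incentive contrast between groups 1 and 2 is kept.
2. **Assessment payment.** Make any payment for the 4-week assessment identical in all four arms.
3. **Consistency.** Reconcile Intervention group: overview, Recruitment, and Outcomes and data collection on who is paid, when and for what.
4. **Analysis text.** Reword the attrition sentence so that intention-to-treat states only who is analysed and in which arm. Then say that all randomised participants are analysed with a method that uses the baseline scores already collected: a likelihood-based model of baseline and week-4 scores, or multiple imputation. Either relies on dropout being explained by what was observed; details can go in the analysis plan.

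The cost is rewording. Group 1's 4-week completion may fall slightly towards that of the other arms, and an added equal assessment payment, if one is chosen, has to be budgeted.
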